### Outcomes

2.4

The primary outcome measures include mental status and water brash before and after surgery. Mental status will be assessed using HADS, which contains both anxiety and depression subscale scores.^[15]^ Water brash will be assessed using the 10-item Eating Assessment Tool (EAT-10), Esophagus and Stomach Surgery Symptom Scale (ES4) and videofluoroscopy swallowing measurement. EAT-10 is a screening assessment scale for dysphagia.^[22]^ ES4 measures the postoperative symptoms of esophagogastric cancer.^[23]^

Secondary outcome measures include the incidence of aspiration pneumonia, number of postoperative hospitalization days, abdominal gas volume, plasma inflammatory markers, chest computed tomography findings, nutritional status, and laboratory examination findings. Aspiration pneumonia will be diagnosed based on the clinical practice guideline for pneumonia.^[24]^ Abdominal gas volume will be measured by analyzing an abdominal radiograph using Koide methods with Image J.^[25,26]^ White blood cell count, serum interleukin-6, tumor necrosis factor α, and granulocyte-colony stimulating factor will be measured as inflammatory markers. Serum albumin, prealbumin, total cholesterol, retinol-binding protein, transferrin, C-reactive protein, and lymphocytes will be measured as nutrition status markers. We will also evaluate body weight, body mass index, triceps skinfolds, and arm muscle circumference measured using bioelectrical impedance analysis (InBody 770, InBody, Soul, Korea).

Secondary safety measurements will include adverse events, side effects of BRIHK, and laboratory data abnormalities exceeding postoperative change. BRIHK has a possible side effect of hypersensitivity (e.g., rash or urticaria).^[15]^ We will routinely examine the laboratory data for postoperative adverse events such as those involving liver function, kidney function, electrolytes, creatine phosphokinase, glucose, and brain natriuretic peptide.

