### Sample size

2.6

There is no clinical evidence regarding the treatment effects of BRIHK for anxiety or water brash. Therefore, we will estimate the appropriate sample size based on feasibility instead of on statistics.

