### Recruitment

2.7

Twenty-four Participants will be recruited from outpatients in the esophagus-stomach surgery department at Tohoku University Hospital, Sendai, Japan.

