### Randomization, allocation, and blinding

2.8

Registration and allocation of the participants will be performed by the investigators and WDB Clinical Research Co., Ltd. The eligible patients will be blindly randomized to either arm P or arm A in a 1:1 ratio. The random sequence will be created using computer-generated permuted block randomization.

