### Statistical methods

2.11

The primary statistical analyses will be performed by WDB Clinical Research Co., Ltd. using the full analysis data set, from which patients who withdraw consent before assessment of the primary endpoint will be excluded. In addition, we will repeat the analyses in the per-protocol set, which will exclude patients with major protocol deviation. The safety analysis will be performed using the complete data set in the BRIHK group.

For baseline characteristics variables, summary statistics will be calculated using frequencies and proportions for categorical data; means, standard deviations, medians, and quartiles will be used for continuous values. Patient characteristics will be compared using the Chi-squared test or Fisher exact test for categorical valuables and the Wilcoxon rank-sum test for continuous valuables. For the primary intra-group analysis, we will calculate mean HADS and ES-4 scores for each timepoint with 95% confidential intervals and compare the HADS and ES-4 scores at the baseline with those during the treatment period using Wilcoxon signed-rank test. For the inter-group analysis, we will calculate the change in the HADS and ES-4 scores from the pre- to post-treatment period and compare them between the 2 groups using Wilcoxon signed rank test. Then, we will perform an analysis of covariance with the covariates of patient characteristics and calculate the confidence interval. For the analyses of secondary outcome measures between the 2 groups, we will perform the Chi-squared test or Fisher exact test for categorical valuables and Wilcoxon rank-sum test for continuous valuables. *P* values less than 5% will be considered statistically significant, and we will not adjust *P* values in multiple comparisons.

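### HADS and ES-4 are first compared between arms on unadjusted change scores, and the ANCOVA that follows does not name the baseline score, which gives up precision in a 24-patient trial unless the pre-post correlation is high

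*Protocol article*

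**What the plan says.** Section 2.11 (Statistical methods) of the protocol article sets out the inter-group analysis of the primary scores in two steps.

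- **Step one:** "we will calculate the change in the HADS and ES-4 scores from the pre- to post-treatment period". The two arms are then compared on this change with a Wilcoxon test that has no covariates.
- **Step two:** "we will perform an analysis of covariance with the covariates of patient characteristics and calculate the confidence interval". The covariates are neither listed nor limited in number, and the dependent variable is not stated. This is the only inter-group analysis of these scores that is given a confidence interval.

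The baseline HADS or ES-4 score is not named as a covariate, and nothing says that it is left out. Section 2.9 (Data collection) lists patient characteristics as an item apart from the HADS, EAT-10 and ES4 forms. That suggests the baseline score may not be meant, but does not settle it.

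The setting is small. Section 2.7 says "Twenty-four Participants will be recruited from outpatients in the esophagus-stomach surgery department", section 2.8 allocates 1:1, and section 2.6 says "we will estimate the appropriate sample size based on feasibility instead of on statistics".

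**The concern.** A raw change score takes the whole baseline value off the follow-up value, as if a patient one point higher at baseline were expected to be one point higher afterwards. When the pre-post correlation is well below 1, this over-corrects and adds baseline noise to the outcome. A patient who starts high also tends to show a larger fall, so a chance difference in baseline between two arms of 12 carries over into the change comparison.

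ANCOVA with the baseline score as covariate estimates the right amount of correction from the data. The plan collects what is needed, but does not commit to this adjustment in either step. Since the sample size was set by feasibility, there is no margin to absorb avoidable loss of precision. The width of the interval for the treatment effect is what is at stake.

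**Working it through.** **Inputs.** N = 24, 12 per arm (sections 2.7 and 2.8). Significance level 5% without multiplicity adjustment (section 2.11), taken as two-sided because sidedness is not stated. The pre-post correlation ρ is not in the document and is varied from 0.3 to 0.9. Equal variances before and after treatment are also assumed, with the score's SD set to 1.

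**The plan's own figure.** The 24 has no effect size, SD or power behind it, so there is nothing to reproduce. For context, the difference detectable with 80% power is (1.96 + 0.84) × √(2/12) = 1.14 SD of whatever variable is analysed.

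**Formulas, per patient.**
- Change score: variance 2(1 − ρ).
- ANCOVA on baseline: variance (1 − ρ²), times 1 + k/(N − k − 3) for k estimated covariates. With k = 1 the factor is 1 + 1/20 = 1.05.
- Ratio of ANCOVA to change score: 1.05 × (1 + ρ)/2.

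| Assumed ρ | Change score | ANCOVA | Ratio | Patients needed with change scores to match (24 ÷ ratio) |
|---|---|---|---|---|
| 0.3 | 1.40 | 0.956 | 0.68 | 35.2 |
| 0.5 | 1.00 | 0.788 | 0.79 | 30.5 |
| 0.7 | 0.60 | 0.536 | 0.89 | 26.9 |
| 0.8 | 0.40 | 0.378 | 0.945 | 25.4 |
| 0.9 | 0.20 | 0.200 | 1.00 | 24.1 |

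The break-even point is ρ = 2/1.05 − 1 = 0.90.

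**Detectable difference** (80% power, in SDs of the score), change score against ANCOVA: 1.35 against 1.12 at ρ = 0.3, 1.14 against 1.02 at 0.5, and 0.89 against 0.84 at 0.7.

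**Simulation check.** The formulas concern means, while the plan uses a rank test on change. Simulated normal data with 12 per arm gave variance ratios of 0.68, 0.78 and 0.91 at ρ = 0.3, 0.5 and 0.7, in line with the formula. For an illustrative 1-SD effect, power with a rank-sum test on change against ANCOVA was 48% against 67%, 61% against 75%, and 83% against 89%.

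**Chance imbalance.** The baseline difference between arms has a standard deviation of √(2/12) = 0.41 SD. Given an imbalance of that size, the change comparison shifts by (1 − ρ) × 0.41, which is 0.29, 0.20 and 0.12 SD at ρ = 0.3, 0.5 and 0.7. Over repeated randomisations these shifts average to zero.

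**Effect of the equal-variance assumption.** In general the change score's extra variance is s₀²(1 − β)², where s₀² is the baseline variance and β the slope of follow-up on baseline. Entry requires a HADS score of at least 8 (section 2.2.1), which may narrow the baseline spread and so shrink this term. For example, with β = 0.5, residual variance 0.75 and s₀² halved to 0.5, the change variance is 0.75 + 0.5 × 0.25 = 0.875, and the ratio is 0.7875/0.875 = 0.90 instead of 0.79. The gain for HADS may therefore be smaller than the table shows.

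**The case against.** The best answer is that the article may already plan the right analysis. Section 2.11 opens that paragraph with baseline characteristics and then speaks of patient characteristics, so a baseline score could fall under the term. If it does, ANCOVA on the change and ANCOVA on the post-treatment score give the same treatment effect, and the loss is confined to the unadjusted Wilcoxon step. An unlisted covariate set is also detail that a condensed article leaves to the full protocol or analysis plan. Both points stand: a reader might infer that the ANCOVA adjusts for patient characteristics in place of the baseline score, but the text makes no such exclusion, and the missing list alone is no error.

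Other stronger readings also fail.

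- **Bias.** The arms are formed by 1:1 randomisation, so the change comparison is biased only conditionally on the imbalance that happens to occur.
- **Covariates chosen by p-value.** The section does say "Patient characteristics will be compared using the Chi-squared test or Fisher exact test", but nowhere links those tests to the choice of covariates.
- **Too many covariates.** Five uninformative covariates would widen the interval by 17% and ten by 45% at N = 24, but nothing in the document points to such numbers.
- **A weak preoperative ES4 score.** Section 2.4 says "ES4 measures the postoperative symptoms of esophagogastric cancer", which makes a low correlation conceivable, but no figure supports it.

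It is also fair that a rank test followed by a supporting ANCOVA is inefficient rather than invalid, and that no stated power is undermined because none is claimed. What remains is that the text fixes an unadjusted change score as the first comparison and does not commit to baseline adjustment in the second.

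**Conclusion.** The point holds as one about precision. The unadjusted change-score step is what the plan states, and the adjusted step does not name the one covariate most likely to matter. Under equal variances, baseline adjustment would cut the variance by about 32%, 21% and 11% at ρ = 0.3, 0.5 and 0.7, by about 5% at 0.8, and by nothing near 0.9. At ρ = 0.5, 24 patients do the work of about 30. The size rests wholly on an assumed ρ and on roughly equal variances before and after treatment, which is doubtful for a scale of postoperative symptoms and for a HADS baseline cut at 8. For ρ below about 0.9 under that model, the direction is secure. The conclusion is not that the comparison is invalid or biased on average, nor that the baseline score has been ruled out of the ANCOVA.

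**What to change.** Make the main inter-group estimate for each scale an ANCOVA of the post-treatment score on arm, with that scale's own baseline score as covariate and a 95% confidence interval. Allow at most one other covariate, named in advance; two covariates cost a variance factor of 1 + 2/19 = 1.11, against 1.05 for one. Keep a two-sample rank test on change as a sensitivity analysis, and name it as the rank-sum test: section 2.11 currently gives the signed-rank test, a paired test, for this comparison of independent arms.

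The change is one of wording and needs no new data. Its price is one residual degree of freedom (21 instead of 22) and reliance on a linear model in a small sample, which the rank-based sensitivity analysis covers. Dropping the baseline significance tests in favour of descriptive tables is optional and not part of the error.

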### Data collection

2.9

All data will be collected and recorded on a paper-based case report form by the investigators. Patient characteristics, the questionnaires, and evaluation forms such as HADS, EAT-10, ES4, as well as the findings of videofluoroscopy swallowing measurement and CT, abdominal gas volume, laboratory data, and physical status will be collected. Adverse effects will also be recorded. After recording the data, the investigators will confirm the case report form, referring to its source documents.

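### Continuous secondary outcomes get an unadjusted rank-sum test with no stated use of the preoperative value, which costs precision at 12 per arm for traits stable within a patient

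*Protocol article*

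**What the plan says.** Section 2.11 of the protocol article gives two different rules for comparing the arms.

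- **HADS and ES-4:** "we will calculate the change in the HADS and ES-4 scores from the pre- to post-treatment period and compare them between the 2 groups". An analysis of covariance on patient characteristics, with a confidence interval, follows.
- **Secondary outcomes:** "secondary outcome measures between the 2 groups, we will perform the Chi-squared test or Fisher exact test for categorical valuables and Wilcoxon rank-sum test", where the rank-sum test is for the continuous ones. No change score, covariate, baseline value or time point is mentioned.

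The continuous secondary outcomes in section 2.4 include postoperative hospital days, abdominal gas volume, inflammatory markers, serum nutrition markers and body measures: "We will also evaluate body weight, body mass index, triceps skinfolds, and arm muscle circumference measured using bioelectrical impedance analysis". Section 2.9 confirms that such data are gathered ("abdominal gas volume, laboratory data, and physical status will be collected") but not when. The schedule is in Figure 2, which is not available here.

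On size, section 2.7 says "Twenty-four Participants will be recruited from outpatients in the esophagus-stomach surgery department", section 2.8 has patients "blindly randomized to either arm P or arm A in a 1:1 ratio", and section 2.6 says "we will estimate the appropriate sample size based on feasibility instead of on statistics".

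**The concern.** Body weight, BMI, skinfold thickness and arm muscle circumference differ widely between patients but usually change little within one patient over a few weeks. If only follow-up values are compared, that between-patient spread stays in the error term. With 12 per arm, the comparison may then be too imprecise to show a difference that the same data could show once each patient's own starting value is used.

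The plan takes account of change for its two primary scores but writes nothing equivalent for the secondary measures. What is at stake is the precision of the nutrition, body-composition and similar results, and how far a null finding among them can be interpreted.

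**Working it through.** The plan has no power figure to reproduce, because the sample size rests on feasibility.

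**Inputs from the article.** There are 24 patients at 1:1, so 24 / 2 = 12 per arm before any dropout. For significance, P "values less than 5% will be considered statistically significant, and we will not adjust" for multiplicity. Sidedness is not stated, so two-sided 5% is assumed.

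**Assumptions.** The data are normal with SD 1 before and after treatment. The pre/post correlation ρ runs from 0.3 to 0.95. A preoperative value exists. The article gives no SD, correlation or expected effect.

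**Step 1: error SD under each analysis.**
- Follow-up value alone: 1.
- Change score: √(2(1 − ρ)).
- ANCOVA on own baseline: √(1 − ρ²).

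**Step 2: difference detectable with 80% power.** By the normal approximation this is (1.96 + 0.84) × √(2/12) × error SD = 1.14 × error SD.

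| ρ | Follow-up alone | Change score | ANCOVA |
|---|---|---|---|
| 0.3 | 1.14 | 1.35 | 1.09 |
| 0.5 | 1.14 | 1.14 | 0.99 |
| 0.7 | 1.14 | 0.89 | 0.82 |
| 0.9 | 1.14 | 0.51 | 0.50 |
| 0.95 | 1.14 | 0.36 | 0.36 |

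For example, at ρ = 0.7, √(1 − 0.49) = 0.714, and 1.14 × 0.714 = 0.82. The noncentral t distribution gives 1.20 instead of 1.14 for follow-up values, with the same pattern: 1.04, 0.86, 0.52 and 0.37 for ANCOVA at ρ = 0.5, 0.7, 0.9 and 0.95.

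**Step 3: simulated power for a true difference of 0.5 SD** (10,000 trials per setting; Monte Carlo standard error at most √(0.25/10,000) = 0.5 percentage points).

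| ρ | Rank-sum, follow-up | Rank-sum, change | ANCOVA |
|---|---|---|---|
| 0.3 | 20% | 15% | 22% |
| 0.5 | 20% | 19% | 26% |
| 0.7 | 20% | 30% | 36% |
| 0.9 | 19% | 71% | 75% |
| 0.95 | 20% | 94% | 95% |

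About one point of the ANCOVA advantage comes from the normal data and not from the baseline: at ρ = 0 the figures are 20% for rank-sum on follow-up values and 21% for ANCOVA.

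**Step 4: validity.** With no true difference, the rank-sum test on follow-up values rejected in 4.4% to 4.7% of trials.

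**Step 5: the gain as sample size.** By the same approximation, 80% power at 0.5 SD needs 2 × (2.80 / 0.5)² = 63 per arm on follow-up values. ANCOVA needs 48 at ρ = 0.5, 33 at 0.7 and 12 at 0.9.

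**The case against.** The strongest answer is that the article names a test, not the quantity tested. A rank-sum test can be run on changes as easily as on follow-up values, and the derived variable and time point may sit in the full protocol or analysis plan. This stands in part: comparison of follow-up values is an inference. It is still the natural one. The same paragraph spells out change for HADS and ES-4 and drops it for the secondary outcomes, whose rule nearly repeats the one for baseline characteristics, where the variable itself is tested. On either reading the named test carries no covariate, so an analysis plan using ANCOVA here would depart from it.

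Second, a preoperative measurement of each variable cannot be confirmed without Figure 2, and hospital days have none. This stands and limits the fix.

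Third, a reader might infer that chance baseline differences produce false effects, or that differences between patients swamp any drug effect. The documents support neither. Randomisation keeps the comparison unbiased, and the test holds its error rate. Arms of 12 will differ by more than 0.5 SD at baseline in 2 × (1 − Φ(0.5/√(2/12))) = 22% of randomisations. That is ordinary chance imbalance, already allowed for in the test, and it reaches the follow-up comparison only in proportion to ρ. With no SD, correlation or expected effect given, swamping cannot be shown.

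Fourth, the gain is uneven. At ρ = 0.3, which may fit cytokines after major surgery, it is about two points.

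**Conclusion.** The point holds as one of efficiency. The protocol fixes an unadjusted rank-sum test for continuous secondary outcomes and writes no use of the preoperative value. If follow-up values are compared, power at 0.5 SD stays near 20% whatever the correlation. ANCOVA would raise it moderately at ρ = 0.7 and to roughly three-quarters at 0.9. If changes are compared, ANCOVA still does better, but only by about 4 to 7 points for ρ from 0.3 to 0.9.

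The stated analysis is not invalid or biased. The size of the loss depends on assumed correlations and SDs, normal data, full retention of 12 per arm, and preoperative values being available. High correlation is most plausible for the body measures and least assured for the inflammatory markers. For secondary outcomes in a trial sized on feasibility, this is a worthwhile improvement and not a threat to the trial.

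**What to change.** For each continuous secondary outcome with a preoperative value, make the between-arm analysis an ANCOVA of the postoperative value, at a stated time point, on arm and that variable's own preoperative value. Since section 2.3 starts dosing before surgery, use a value taken before the first dose; a later one could already reflect treatment. For skewed markers such as cytokines, work on the log scale or use Quade's rank ANCOVA. Report the adjusted difference with its 95% CI (as a ratio if logged). Keep the rank-sum test for outcomes with no preoperative value, such as postoperative hospital days.

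This changes analysis wording only, with no added patients. Visits do not change either, provided the preoperative values are already scheduled. It costs one degree of freedom per model and a little more analysis work.

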### Data monitoring

2.12

To oversee the progress of the trial and to ensure that the study is conducted and data are handled in accordance with the protocol and applicable ethical and regulatory requirements, independent data monitor members from the sponsor and competing interests will be appointed. On/off-site risk-based monitoring will be conducted when the first participant is registered, when the 10^th^ participant is registered, and when all of the participants complete the study protocol. On-site monitoring for the storage of data documents will be conducted at both the start and end of this study.

### Harms

2.13

The adverse events, which include solicited adverse events, spontaneously reported adverse events, and other unintended effects of trial interventions, will be investigated. A follow-up investigation of the adverse events will be conducted, and we will report the outcome to the data and safety monitoring board to assess the causal association with the intervention. Severe adverse events with causal association must be reported to the relevant departments.

### Auditing

2.14

To assess and assure the reliability and integrity of the study, an independent auditor from the sponsor and competing interests will be appointed. Auditing will be conducted after data collection is completed.

### Ethics and dissemination

2.15

This trial complies with the Declaration of Helsinki and JP Clinical Trial Act.^[27]^ It was designed as a specified clinical trial and will be conducted by Tohoku University Hospital with approval from the Japanese Ministry of Health, Labour and Welfare certified clinical research review board, Tohoku University (CRB2180001).

### Trial status

2.16

The protocol and progress are registered on the Japan Registry of Clinical Trials (jRCT s021190001) and University Hospital Medical Information Network (UMIN000031330). Recruitment will begin in April 2019 and is expected to be completed in May 2023. The most recent version of the protocol (ver. 2.1) was approved by the Japanese Ministry of Health, Labour and Welfare certified clinical research review board, Tohoku University (CRB2180001).

## Discussion

3

In this single-center, randomized controlled clinical trial, we aim to evaluate whether BRIHK is effective for alleviating anxiety and preventing aspiration in the postoperative period in esophageal cancer patients. To date, no clinical trial has been conducted on orally administered drugs, such as Kampo medicine, which could improve anxiety and water brash in the perioperative period of esophageal cancer surgery. The results of this study will be published as a research article, and provide evidence of BRIHK for beneficial mental and physical effects in perioperative esophageal cancer patients.

Hangekobokuto has multiple functions for aspiration, abdominal symptoms, and anxiety, as follows: hangekobokuto administration reduced substance P activity and improved the cough reflex in patients with a history of aspiration pneumonia.^[16]^ Oikawa et al reported that hangekobokuto administration in functional dyspepsia patients decreased abdominal gas volume and symptoms of abdominal pain, indigestion, and constipation.^[28]^ Magnolia officinalis bark, a crude drug component of BRIHK and hangekobokuto, contains an anxiolytic-like agent (4-metylhobokiol) that enhances GABAergic transmission.^[29]^ In addition, we have recently shown that BRIHK ameliorated the delayed gastric emptying induced by corticotropin-releasing factor in a rodent model. BRIHK may not only enhance gastric emptying, but also suppress the corticotropin-releasing factor pathway through acetylcholinesterase, dopamine D2/D3 receptor, and neuropeptide Y Y2 receptor.^[30]^ Therefore, BRIHK could improve aspiration, gastric movement, and anxiety through multiple mechanisms.

In traditional Kampo theory, BRIHK, as well as hangekobokuto, is used for the treatment of “qi stagnation pattern,” which is characterized by a sensation of obstruction in the throat, a sensation of ear-tube obstruction, fullness in the chest, hypochondrium or abdominal distension, a depressive state, or pain.^[31]^ Gastric dysmotility and mental distress in the perioperative period are usually thought to be symptoms of “qi stagnation pattern.” Our study will provide an integrative approach using the standard surgical procedure together with Kampo medicine.
